## 5. STUDY TREATMENTS

### 5.1 Assigning Subjects to Treatments and Blinding

#### 5.1.1 Administration Arms/Treatment Sequence

##### Investigational product group

DS-5670d: A single dose of 0.6 mL (DS-5670d 60 µg as mRNA) will be intramuscularly administered to the deltoid muscle of the upper arm.

##### Comparator group

Comirnaty RTU IM: A single dose of Comirnaty RTU IM at a volume of 0.3 mL will be intramuscularly administered to the deltoid muscle of the upper arm.

#### 5.1.2 Method of Treatment Allocation

The independent biostatistician will prepare a subject randomization list showing a correspondence between subject numbers and study drugs (investigational product or comparator).

Subjects will be randomized in a 1:1 ratio to the DS-5670d group or Comirnaty RTU IM group, with study site, age (12 to 17 years, 18 to 64 years, 65 years and older), the presence or absence of a history of SARS-CoV-2 infection (yes, no), the presence or absence of a history of vaccination with SARS-CoV-2 vaccine (yes, no) as stratification factors based on the information entered in the Interactive Response Technology (IRT). The presence or absence of a history of SARS-CoV-2 infection used as a stratification factor will be based on the history of SARS-CoV-2 infection reported by the subject or legal representative at informed consent (self-reported SARS-CoV-2 infection history) and the SARS-CoV-2 antibody test result from the rapid test kit at the time of eligibility evaluation. A subject will be defined as having a history of SARS-CoV-2 infection if he/she is determined to have a self-reported SARS-CoV-2 infection history at informed consent or have a positive SARS-CoV-2 antibody with the rapid test kit at the time of eligibility evaluation. Otherwise, the subject will be defined as having no history of SARS-CoV-2 infection.

The procedures for subject enrollment are shown in [Figure 5.1-1](#).

After obtaining written consent from the subject or subject's legal representative, the investigator or subinvestigator will prepare a subject screening list, and confirm the eligibility of the subject.

The investigator, subinvestigator, or study staff will register the required information in the IRT after obtaining informed consent. The IRT will allocate a study-specific subject number. The investigator, subinvestigator, or study staff will enter confirmation of the subject eligibility in the IRT. The IRT will randomize the eligible subject to an administration and notification of the assigned study drug will be sent to the unblinded personnel at the study site (See Section 5.1.3).

After the unblinded personnel at the study site (study drug manager or study drug management assistant designated by the study drug manager, study drug preparer, and study drug administration personnel) will confirm the assigned study drug based on the IRT notification, the assigned study

Confidential

drug will be dispensed, prepared and administered in a separate location from the blinded personnel. The date of the randomization is defined as the enrollment date.

If the subject is determined ineligible, the investigator or subinvestigator will provide the subject and, if necessary, his/her legal representative with the reason for the ineligibility. The investigator or subinvestigator will also record the reason for not enrolling the subject in the subject screening list.

Figure 5.1-1 Subject Enrollment Procedure

[figure not shown]

### 5.1.3 Blinding

In this study, the "observer-blind approach" is adopted (the reason for using this approach is detailed in Section 3.2 "Rationale of Study Design").

Unblinding will be applied to the independent biostatistician, study drug manager or study drug management assistant (designated by the study drug manager), study drug preparer, study drug administration personnel, unblinded study staff (if needed), and unblinded sponsor personnel (including unblinded monitor). Blinding will be applied to subjects, legal representatives, investigator, subinvestigator, study staff, nurses, monitors, the sponsor, and personnel measuring antibody titers.

The unblinded and blinded personnel must keep independent of each other. The unblinded personnel must not disclose information to maintain the blinding to the blinded personnel. An unblinded personnel cannot have the role of the blinded personnel.

When documenting assignment of each subject in the source documents, etc., the unblinded personnel should make sure that the administered study drug is not identifiable. If the blinded personnel become aware of the subject's assignment details, the sponsor personnel will be notified immediately.

#### 5.1.4 Emergency Unblinding Procedure

In the case of an emergency where, in the opinion of the investigator or subinvestigator, the study administration must be unblinded in order to evaluate a course of medical treatment, the investigator or subinvestigator can perform the unblinding by using the IRT. Entry of the AE electronic case report form (eCRF) page must be completed before the unblinding except in cases where immediate treatment of the subject is required. If immediate treatment is required, the AE eCRF page is to be completed within 24 hours of the unblinding.

In the event of an unblinding, the subject and designated study site staff/personnel who are providing immediate care to the subject will be informed about their study drug assigned. The unblinding results must not be included in the subject's source documents to ensure the treatment assignment will remain blinded to monitor and other study personnel not involved with the subject's immediate care.

In the event of an unblinding, an automatic notification (via e-mail) will be sent to the investigator or subinvestigator and selected sponsor personnel from the IRT vendor. The notification will contain the name of a person who broke the blinding, the date and time of unblinding, and the subject number. The notification will not contain any unblinding information.

Once study treatment has been unblinded for a specific subject, the investigator or subinvestigator should treat the subject appropriately. The investigator or subinvestigator will perform evaluations at the end of study drug administration and follow-up evaluations for the subject in accordance with the protocol.

### 5.2 Drugs Used in the Study

"Drugs used in the study" refer to drugs (including investigational product) containing the approved active ingredient or unapproved active ingredients specified in the clinical trial plan notification and this protocol that are used to evaluate the efficacy and safety of the investigational product in the study. Specifically, study drugs (investigational product and comparator), concomitant medications, rescue drugs, premedication, etc. are included.

Drugs used in the study are the investigational product (DS-5670d) and the comparator (Comirnaty RTU IM). Since drugs other than the study drugs will not be used in the study, the "drug used in the study" is described as "study drug" in this protocol.

#### 5.2.1 Description

Investigational product

DS-5670d

- 1) Test substance identification code: DS-5670d
- 2) Generic name: To be determined.
- 3) Content and dosage form:

Confidential

A whitish turbid aqueous injection containing MAFB-7256a (DS-5670 mRNA) encoding the RBD of the S protein of the Omicron strain XBB.1.5 encapsulated in LNP (LNP-mRNA) filled in a colorless glass vial. A solution containing the equivalent of 60 µg of MAFB-7256a in a drug solution of 0.6 mL in a vial (labeled volume: 1.5 mL).

- 4) Lot number: Lot number is provided in the "Pharmacy Manual."

For details and the handling of the investigational product, refer to the "Investigator's Brochure (IB)" and "Pharmacy Manual."

## Comparator

Comirnaty RTU IM

- 1) Brand name: COMIRNATY RTU intramuscular injection
- 2) Generic name: Coronavirus (SARS-CoV-2) RNA vaccine
- 3) Content and dosage form: A frozen aqueous solution containing 0.225 mg of raxtozinameran encapsulated in LNP-mRNA filled in a colorless glass vial (labeled volume 2.25 mL).
- 4) Lot number: Lot number is provided in the "Pharmacy Manual."

For details and the handling of comparator, refer to the "Pharmacy Manual."

## 5.2.2 Labeling and Packaging

Details on the packaging and labeling of the study drug are described in the "Pharmacy Manual."

## 5.2.3 Preparation

Details of the study drug preparation method are explained in the "Study Drug Preparation and Administration Procedures." Since this study is conducted with an observer-blind approach, the study drug preparer and study drug administration personnel must not disclose information that can identify the study drug to the blinded study personnel until unblinding.

## 5.2.4 Administration

The study drug will be administered to subjects according to the procedure described below. In principle, the study drug should be administered on the non-dominant arm.

- 1) The unblinded personnel at the study site (study drug manager or study drug management assistant designated by the study drug manager, study drug preparer, study drug administration personnel) will confirm and dispense the assigned study drug based on the IRT notification.
- 2) The study drug preparer will prepare the study drug in a separate location from the

Confidential

blinded personnel.

- 3) The study drug administration personnel will administer the study drug to subjects in a manner that the blinded personnel cannot identify the administered study drug.

## 5.2.5 Storage

### Investigational product

- DS-5670d

At 2°C to 8°C, shielded from light

### Comparator

- Comirnaty RTU IM

−90°C to −60°C

Refrigerated: At 2°C to 8°C for 10 weeks\*

\*: Thawed vials should not be refrozen, and should be used within the shelf life.

## 5.3 Drugs Used in the Study Other Investigational Drugs

Not applicable.

## 5.4 Drug Accountability

### 5.4.1 Study Drugs Supplied by the Sponsor

The study drug should be managed in accordance with the "Pharmacy Manual."

The sponsor will supply the investigational product to the study site after execution of the study contract. The Ministry of Health, Labour and Welfare will supply Comirnaty RTU IM to the study drug storage depot designated by the sponsor. The sponsor will supply Comirnaty RTU IM to the study site after execution of the study contract. The study drug manager or the study drug management assistant designated by the study drug manager will receive the investigational product and Comirnaty RTU IM, and check the amount and condition of the received drugs. The sponsor should be contacted as soon as possible if there is a problem during the shipment. A study drug accountability list will be prepared for the investigational product and comparator, and must be kept current.

At the end of the study or as directed by the sponsor, unused study drugs will be returned to the sponsor. Study drugs will be returned after the monitor has completed confirmation and reconciliation of the amount of remaining unused study drugs based on the study drug accountability list. At the end of the study, the investigator or the study drug manager will prepare a copy of the final study drug accountability list and submit it to the sponsor.

#### 5.4.2 Study Drugs Not Supplied by the Sponsor

Not applicable.

### 5.5 Temporary Dose Discontinuation and Reduction

If any significant abnormality is observed in the subject during study drug administration, the administration should be immediately discontinued.

### 5.6 Method of Confirming Administration Compliance

The investigator or subinvestigator will perform medical examinations and measure axillary body temperature of the subject before study drug administration to determine the subject's eligibility for study drug administration. If the subject has a fever of  $\geq 37.5^{\circ}\text{C}$  or suffers from a serious acute disease, study drug should be discontinued. The investigator or subinvestigator will record the date of determination of the subject's eligibility for study drug administration, the actual value of body temperature measured for eligibility evaluation or confirmation of administration compliance, and the result of the determination (acceptable or unacceptable) in the eCRF.

### 5.7 Prior Treatments and Concomitant Therapies

If any concomitant medication is used during the period from study drug administration to the study visit at 4 weeks after study drug administration, the investigator or subinvestigator will record the drug name, dosage regimen, route, start date, end date, and reason for use in the eCRF. If any concomitant therapy is used during the period from study drug administration to the study visit at 4 weeks after study drug administration, the investigator or subinvestigator will record the therapy name, frequency, start date, end date, and reason for the therapy in the eCRF.

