#### 5.7.1 Prohibited Concomitant Medication/Therapy

The use of the following concomitant medications and therapies will be prohibited for 4 weeks after study drug administration. However, this does not apply when the investigator or subinvestigator determines that treatment is necessary for AE that occurs after obtaining informed consent.

- 1) Blood transfusions (including component transfusions)
- 2) Gamma globulin preparations
- 3) Systemic administration of immunosuppressive drugs (including treatments to autoimmune diseases)
- 4) Immunosuppressive therapy (including radiotherapy)
- 5) Hematopoietic agents (except for iron and vitamin preparations)
- 6) Systemic corticosteroids (excluding external agents and inhalants)
- 7) Preventive antipyretic analgesics\*
- 8) Other vaccines (excluding influenza vaccines)

Confidential

9) Other drugs used in the study

\*: The use of these drugs for prevention of fever and pain will be prohibited.

<Rationale>

- 1) to 6) These were included because these drugs/therapies may influence the immunogenicity evaluation of the study drug.
- 7) This was included because these drugs may influence the safety evaluation of the study drug.
- 8) This was included because these vaccines may influence the immunogenicity and safety evaluation of the study drug.
- 9) This was included because the safety of other drugs used in the study under development has not been established, and concomitant use of the study drug with such drugs may cause safety problems.

In addition, the use of SARS-CoV-2 vaccines (including drugs used in the study), except in this study, will be prohibited for 26 weeks after study drug administration.

<Rationale>

The use of SARS-CoV-2 vaccines (including investigational drugs), except in this study, will be prohibited for 26 weeks after study drug administration because they may influence the evaluation of long-term efficacy and safety.

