#### 6.4 Post-dose Evaluation (Day 29, Allowance + 3 Days)

- 1) The subject will be requested to visit the study site for the post-dose evaluation at 4 weeks after study drug administration. The investigator or subinvestigator will confirm the subject's health status by medical interview and review the descriptions in the electronic diary to determine the seriousness, severity, and causality of nonserious unsolicited AEs, SAEs, and AEs leading to withdrawal from the study during the period from study drug administration to the study visit for the post-dose evaluation at 4 weeks after study drug administration in accordance with the definitions in Section 9.3, and record the results on the AE page of the eCRF. The use of concomitant medications/therapies during the period from study drug administration to the study visit for the post-dose evaluation at 4 weeks after study drug administration will also be confirmed.
- 2) The investigator or subinvestigator will perform the following investigations, observations, and examinations, and document them in the eCRF.
  - Blood sampling for immunogenicity evaluation
  - Clinical laboratory tests (blood/urine)
  - Pregnancy test (urine)\*
  - SARS-CoV-2 antibody test (to be performed at the central laboratory)
- 3) The investigator or subinvestigator will confirm that all data in the electronic diary have been transferred and then confirm that the application for data entry has been uninstalled from the electronic diary entry device. If a device has been lent to the subject or legal representative, the investigator or subinvestigator will collect the device.

\*: For women of childbearing potential only.

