#### 6.5 Follow-up Examination (Day 57 [Allowance $\pm$ 7 Days], Day 85 [Allowance $\pm$ 7 Days], Day 113 [Allowance $\pm$ 7 Days], Day 141 [Allowance $\pm$ 7 Days], and Day 183 [Allowance $\pm$ 14 Days])

The subject will visit the study site on Day 57, Day 85, Day 113, Day 141, and Day 183. The investigator or subinvestigator will perform the following investigations, observations, and examinations, and document them in the eCRF. For subjects aged 12 to 17 years, only subjects who are able to visit the study site will visit the study site on Days 57, 113, and 141. In addition, if a solicited AE is ongoing at the study visit for the post-dose evaluation, the investigator or subinvestigator will confirm the outcome of the solicited AE, and enter the log number, event term and date of outcome of the event in the electronic diary in the eCRF.

- Blood sampling for immunogenicity evaluation
- SARS-CoV-2 antibody test (to be performed at the central laboratory)

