## 11.2 Analysis Sets

Subjects with major GCP violations (violation of informed consent obtainment and significant violations of study procedures) will be excluded from all analysis sets.

- All subjects enrolled in the study must have signed the informed consent form by the subjects or legal representatives.
- All randomized subjects must have signed the informed consent form by the subjects or legal representatives.
- The safety analysis set will consist of all subjects who have signed the informed consent form by the subjects or legal representatives and received at least one dose of study drug.
- The solicited safety analysis set will consist of all subjects with at least one available data on presence or absence of occurrence of solicited AE in the safety analysis set.

Confidential

- The full analysis set (FAS) will consist of randomized subjects who meet the following criterion:
  - 1) Having received at least one dose of the study drug.
- The per-protocol set (PPS) will consist of subjects included in the FAS who meet all of the following criteria:
  - 1) Having no significant protocol violations that may affect the efficacy evaluation (eg, violation of inclusion/exclusion criteria, prohibited concomitant medications/therapies, violation of withdrawal/discontinuation criteria).
- The FAS for immunogenicity evaluation (FAS for Immunogenicity) will consist of subjects included in the FAS who meet the following criterion:
  - 1) Having immunogenicity measurements before study drug administration and at least one immunogenicity measurement after study drug administration.
- The PPS for immunogenicity evaluation (PPS for Immunogenicity) will consist of subjects included in the FAS for Immunogenicity who meet the following criterion:
  - 1) Having no significant protocol violations that may affect the immunogenicity evaluation (eg, violation of inclusion/exclusion criteria, prohibited concomitant medications/therapies, violation of withdrawal/discontinuation criteria).
- The FAS with basic immunity (Immunized FAS) will consist of subjects included in the FAS who meet the following criterion:
  - 1) Having at least either a history of SARS-CoV-2 infection\* or vaccination with SARS-CoV-2 vaccine and completed the study drug administration as specified in the protocol.

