| Solicited adverse events (AEs)                                                 |                       | ←         | →       |         |         |                    |          |                    |                    |          | (■)                       |
| AEs                                                                            |                       | ←         |         |         | →       |                    |          |                    |                    |          | (■)                       |
| SAEs                                                                           | ←                     |           |         |         |         |                    |          |                    |                    | →        | ■                         |
| Investigation of the onset of COVID-19 b                            |                       | ←         |         |         |         |                    |          |                    |                    | →        | ■                         |
| Prohibition period of other medications and concomitant therapies c | ←                     |           |         |         | →       |                    |          |                    |                    |          |                           |

■: Mandatory, ■: To be performed whenever possible, (■): To be performed depending on the timing of withdrawal from the study.

a: To be performed for women of childbearing potential only.  
b: During the investigation, subjects with symptoms suspected of COVID-19 should be instructed to visit the study site whenever possible and undergo the RT-PCR test using nasopharyngeal swab. For subjects tested for COVID-19 at other medical institutions, the result of the test (eg, RT-PCR, SARS-CoV-2 antigen test) should be obtained at a later date.  
c: Use of SARS-CoV-2 vaccines (including drugs used in the study) will be prohibited during the period from informed consent to 26 weeks after study drug administration.  
d: To be performed for subjects aged 12 to 17 years to the extent possible.

Confidential

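### Outside SARS-CoV-2 vaccination is prohibited for 26 weeks but concomitant products are recorded only to Week 4, so a later vaccination may be missed in the 26-week COVID-19 and titre analyses

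*Protocol*

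**What the plan says.** **The prohibition.** Section 5.7.1 states that SARS-CoV-2 vaccines, "except in this study, will be prohibited for 26 weeks after study drug administration because they may influence the evaluation of long-term efficacy and safety". Footnote c of Table 17.1-1 repeats the rule: their use "will be prohibited during the period from informed consent to 26 weeks after study drug administration".

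**The recording window.** Section 5.7 sets the condition for recording medications as "If any concomitant medication is used during the period from study drug administration to the study visit at 4 weeks after study drug administration" and, in parallel, for therapies as "If any concomitant therapy is used during the period from study drug administration to the study visit at 4 weeks after study drug administration". The Day 29 check in Section 6.4 has the same limit: "The use of concomitant medications/therapies during the period from study drug administration to the study visit for the post-dose evaluation at 4 weeks".

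**The later visits.** On Days 57, 85, 113, 141 and 183, Section 6.5 has the investigator "perform the following investigations, observations, and examinations, and document them in the eCRF". The items are immunogenicity blood and the central-laboratory antibody test, plus the outcome of any solicited adverse event still ongoing. Table 17.1-1 adds SAE collection and investigation of COVID-19 onset up to 26 weeks. The withdrawal visit (Section 6.6) covers AEs, SAEs, COVID-19 and samples. None of these lists a question on outside vaccination. Vaccination history is collected at baseline only (Section 6.1).

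**Use in the analysis.** Section 11.2 gives, among its examples of violations that exclude a subject from the per-protocol sets, "prohibited concomitant medications/therapies, violation of withdrawal/discontinuation criteria". Section 11.4 makes those sets primary for both immunogenicity and COVID-19 incidence.

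**The concern.** The protocol names an exposure that could distort its long-term results, prohibits it for 26 weeks, and makes prohibited products a ground for per-protocol exclusion. It then ends routine collection of that exposure at Week 4. Beyond that point the exclusion works only if the site happens to learn of the vaccination.

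Two results are exposed:

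- **Secondary endpoint.** COVID-19 incidence over 26 weeks, with its Kaplan-Meier curves and incidence ratios (Section 11.4.2.2).
- **Exploratory endpoints.** GMT and seroresponse at Weeks 8, 12, 16, 20 and 26 (Section 2.3.3). The matching objective in Section 2.1.3 is persistence of immune activity after DS-5670d itself. An undetected later vaccine raises that arm's titre whether or not the other arm is equally affected.

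The document gives some reason to think the opportunity exists. XBB.1.5 vaccines were approved in Japan from 20 September 2023 (Section 1.2). Package inserts were revised on 1 April 2024 so that a single dose became possible regardless of history, and a minimum booster interval of 3 months is cited for the comparator's parent vaccine (both Section 3.2).

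**Working it through.** **1. Is any design figure affected?** The point rests on no figure stated in the protocol. The nearest is the Week 4 power in Section 11.6, which reproduces closely.

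- Inputs: 345 per group less 10%, so n = 310; SD 0.533 on the log10 scale; margin −log10(0.67) = 0.1739; one-sided alpha 0.025.
- GMT: standard error 0.533 × √(2/310) = 0.0428; power = Φ(0.1739/0.0428 − 1.96) = 98.2% (stated 98.2%).
- Seroresponse at 80% in both groups: standard error √(2 × 0.8 × 0.2/310) = 0.0321; power = Φ(0.10/0.0321 − 1.96) = 87.5% (stated 87.2%).
- Product: 86.0% (stated 85.6%).

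These endpoints are measured at Week 4, inside the recording window, so nothing here changes.

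**2. Length of the gap.** The prohibition covers 26 weeks after dosing and recording covers 4. The unrecorded part is 26 − 4 = 22 weeks. In days it is 183 − 29 = 154 of 183 − 1 = 182, or 85%.

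**3. Can another procedure fill it?**

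- *Deviation reporting (Section 15.5).* It has no Week 4 limit, but it applies to what the site knows. It creates a duty to report and does not provide a means of detection.
- *AE interviews (Section 9.2).* Subjects are questioned in general terms, nonserious unsolicited AEs are recorded only to Week 4, and a vaccination is not itself an AE.
- *Antibody test (Section 6.11).* The on-site kit is read on anti-N only, and the target of the central assay is not stated. It cannot be relied on to show vaccination, and it gives no date.

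**4. Size for one arm's late GMT (illustration).** The protocol gives neither the share vaccinated, f, nor the fold rise, R, so both are assumed. If a share f of an arm is vaccinated before the sample, undetected, and their titres rise R-fold, the arm's GMT is multiplied by R^f.

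| f | R = 2 | R = 4 | R = 8 |
|---|---|---|---|
| 2% | 1.014 | 1.028 | 1.042 |
| 5% | 1.035 | 1.072 | 1.110 |
| 10% | 1.072 | 1.149 | 1.231 |

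**5. Size for between-arm comparisons with balanced uptake (illustration).**

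- If f and R are the same in both arms, R^f cancels from the GMT ratio.
- If vaccinees in both arms instead reach a common titre, a true ratio t becomes t^(1−f). For t = 0.67 this gives 0.675 (f = 2%), 0.684 (5%) and 0.697 (10%).
- For COVID-19, take a true incidence ratio of 1.5, with 10% of person-time in each arm following an outside vaccination at a common rate of 0.5 times the comparator rate. The observed ratio is (0.9 × 1.5 + 0.1 × 0.5)/(0.9 + 0.1 × 0.5) = 1.40/0.95 = 1.47. At 0.3 times the comparator rate it is 1.38/0.93 = 1.48.

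**The case against.** The strongest reply is that an outside vaccination is a protocol deviation. Section 15.5 requires all deviations to be notified promptly and documented, with no end at Week 4. Section 5.8.1 lists a significant deviation as a reason for withdrawal, and Section 11.2 lets known cases be excluded from the per-protocol sets. The list in Section 6.5 is also not exhaustive, since Table 17.1-1 continues SAE and COVID-19 collection to 26 weeks, and the eCRF itself is not available here. All of this stands for vaccinations that the site learns of. It does not provide a procedure by which the site would learn of them, and the schedule table contains no such item either.

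A reader might infer that late vaccination will contaminate the 26-week results unseen. The documents do not support that. They give no rate of outside vaccination, and known cases must be reported. The supportable statement is that cases may be missed because they are not systematically collected.

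A reader might also assume that uptake will differ between arms and bias the ratios materially. Nothing in the protocol suggests this: subjects are blinded (Section 5.1.3) and both arms receive an active XBB.1.5 mRNA vaccine. Nor does the protocol show that outside vaccines were accessible throughout follow-up, because the study dates are in an attachment that is not shown.

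Finally, rules for excluding titres or censoring follow-up may properly sit in the SAP, so their absence here is no fault. But the SAP cannot apply a date that was never collected, and the collection window is fixed in the protocol.

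**Conclusion.** The mismatch is real and limited in scope. For 22 of the 26 weeks of the prohibition, no listed procedure asks about or dates an outside SARS-CoV-2 vaccination, so removing such subjects from the per-protocol sets depends on ad hoc disclosure. The results at risk are the secondary 26-week COVID-19 incidence and the exploratory Week 8 to 26 titres. The confirmatory Week 4 endpoints, their power and the testing sequence are untouched.

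Under the assumed 2- to 8-fold rise, an arm's late GMT would be inflated by about 4% to 11% at 5% undetected uptake and about 7% to 23% at 10%. These figures assume that every vaccinee was vaccinated before the sample and that none was detected. With balanced uptake the between-arm ratios change little, so the main exposure is the within-arm description of persistence. The actual size cannot be determined from the protocol.

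**What to change.** Add one eCRF item at each visit from Day 57 to Day 183 and at withdrawal: SARS-CoV-2 vaccine received outside the study (yes/no), product and date. Make the change in Sections 5.7, 6.5 and 6.6 and add a row to Table 17.1-1. Leave the general concomitant-medication window at Week 4; Day 29 is already covered by Sections 5.7 and 6.4. The SAP can then use the date for per-protocol exclusion or censoring.

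The cost is one extra question at visits that already take place and a minor amendment. Sample size and power do not change.
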